### Interim analysis

　No interim analysis will be performed in this trial.

### Efficacy Analysis Methods

Primary analysis for the primary endpoint

The primary endpoint (percent change from baseline in total trajectory length) during stimulation (immediately after noisy GVS initiation to 3 h later) will be used as the response variable, and timing (Session I, Session II), treatment device (placebo, noisy GVS), time point, interaction between treatment device and time point, and allocation factors (total trajectory length at screening (per 60 s (<200 cm, ≥200 cm), unilateral/bilateral vestibular impairment) as the explanatory variables and fitting a mixed-effects model with individual effects as a variable effect. The least-squares mean of the treatment effect throughout the stimulation is calculated, and the *P* values are calculated for the 95% confidence interval and the null hypothesis that the treatment effect is 0%. The Kenward–Roger method is used to calculate the degrees of freedom.

　If the sensory threshold is found to be exceeded, a decision on whether to accept or reject the data thereafter will be made at the Case Review Committee.

The point estimates and 95% confidence intervals should be obtained for the least squares means of the rates of change by treatment device and time point calculated by the model above. The trends over time are also shown in the Figure.

Secondary analyses for the primary endpoints:

1. The descriptive statistics are calculated for the raw values of total trajectory length, change from baseline, and rate of change at all the time points by allocation group, treatment stimulus period, and time points. Subsequently, the allocation groups are combined, and descriptive statistics are calculated for each treatment device and time point. The descriptive statistics of the difference in the amount and rate of change within individuals are calculated for each time point, and a one-sample t-test is performed to calculate the *P*-value.
2. Corresponding t-tests will be performed for the difference between the mean rate of change in the total trajectory length from immediately after the start of stimulation to 3 h after stimulation in the GVS period and the mean rate of change in the total trajectory length from immediately after the start of stimulation to 3 h after stimulation in the placebo period.
3. Inference on treatment effects using Bayesian flow methods: A mixed-effects model was fitted with the rate of change in the total trajectory length during stimulation as the response variable, the allocation group, treatment instrument, time point, interaction between treatment instrument and time point, and baseline values as explanatory variables, and individual effects as variable effects to obtain the posterior distribution of least squares means for the treatment effect. The prior distribution is Jeffrey’s uninformed prior distribution, and the posterior probability that the improvement in the GVS period is at least 5%, 10%, or 15% greater than the improvement in the placebo period is calculated. The 95% and 90% confidence intervals for the posterior probabilities are also calculated.
4. A mixed-effects model is fitted with the rate of change in the total trajectory length during stimulation in the GVS period as the response variable and baseline values as the explanatory variables to obtain a posterior distribution of the least-squares mean of the rate of change averaged over time points. The prior distribution is calculated as the posterior probability that there is at least 5%, 10%, 15%, and 20% improvement in the GVS period for the prior distribution obtained from Jeffrey’s uninformative prior distribution and the data up to 3 h after the second period of stimulation in the investigator-initiated clinical trial 3. The 95% and 90% credit intervals of the posterior probabilities will also be calculated.
5. To confirm the validity of the simulation experiment setting in the sample size estimation, correlation coefficients between the rates of change in the total trajectory length during stimulation will be calculated for each treatment device and time point.
6. The same model as in the main analysis for the primary endpoint will be used for the change from the baseline in the total trajectory length during stimulation.
7. The same analyses as the primary and secondary analyses (1) and (2) for the primary endpoint will also be performed using data after the sensory threshold is found to have been exceeded.

Analysis for secondary endpoints

- Analysis for Stabilometry

1. Descriptive statistics will be calculated for the percent change from baseline in the perimeter area and RMS values at all time points by allocation group, treatment stimulus period, and time point. Subsequently, the allocation groups are combined and descriptive statistics are calculated for each treatment device and time point. The descriptive statistics of the difference in the rate of change within individuals will be calculated at each time point, and a one-sample t-test will be performed to calculate the *P*-value.
2. For the rate of change in the total trajectory length, perimeter area, and RMS value in all time points, the mean rate of change and change over time in 95% confidence interval by treatment device and time point will be illustrated.

- Analysis of gait function tests

1. Descriptive statistics will be calculated for the percentage change from baseline in the gait test endpoints (DGI score, walking speed at 10-m gait, stride length, step time, and left-right sway) at all time points by allocation group, treatment stimulus period, and time point. Next, the allocation groups will be combined and descriptive statistics will be calculated for each treatment device and time point. The descriptive statistics of the difference in the rate of change within individuals at each time point will be calculated for each time point for the whole group and for each group, and a t-test between groups will be performed to calculate the *P*-value.
2. The same model as the main analysis for the primary endpoints will be used for the percent change in the perimeter area, RMS values, and gait test endpoints (DGI score, walking speed at 10 m gait, step length, step time, and left-right sway) during stimulation.
3. For the rate of change in endpoints of the gait test in all time points, the mean value of the rate of change and the changes over time in 95% confidence interval by device and time point shall be illustrated.

- Analysis for subjective improvement scores

1. Descriptive statistics will be calculated for subjective improvement scores at all time points by allocation group, treatment stimulus period, and time point. Subsequently, the allocation groups will be combined and descriptive statistics will be calculated by treatment device and time point.
2. With the subjective improvement score during stimulation as the response variable; allocation group, treatment device, and interaction of time point as the explanatory variables; the mixed effect model with individual effect as the random effect is applied. The least squares means of the treatment effects throughout the stimulations is determined, and the 95% confidence intervals and *P*-values are calculated. The Kenward–Roger method is used to calculate the degrees of freedom.
3. For the subjective improvement scores in all the time points, the mean value and changes over time in the 95% confidence interval by treatment device and time point are illustrated.

- Analysis of QOL data

1. Descriptive statistics will be calculated for the change from baseline in the mFES score, DHI score, and DHI subscale scores at all time points by allocation group, treatment stimulus period, and time point. Subsequently, the allocation groups will be combined and descriptive statistics will be calculated by treatment device and time point. Regarding the difference in the amount of change within individuals, the descriptive statistics are calculated by time point and a one-sample t-test will be performed to calculate the *P*-value.
2. An analysis of covariance will be performed using the mFES score, DHI score, and DHI subscale scores at 3 and 7 h after the start of stimulation, respectively, as the response variables, and the allocation group, treatment device, and baseline values as the explanatory variables.

- Examination of correlations between endpoints

1. Pearson/Spearman correlation coefficients between the rate of change in total trajectory length at each time point during stimulation and the following variables are calculated for each treatment device.

- Percentage change in gait test endpoints
- Subjective Improvement Score

1. Pearson/Spearman correlation coefficients between the rate of change in total trajectory length and the following variables are calculated for each treatment device at 3 and 7 h after the start of stimulation, respectively.

- mFES Score
- DHI Score
- Scores for each subscale of DHI
- Number of steps
- Calculation of posterior probabilities

1. For each secondary endpoint, as in the secondary analysis (3) for the primary endpoint, a Bayesian flow technique was used to set the prior distribution as Jeffreys uninformed prior distribution, and the posterior probability that the improvement in the GVS period was at least slightly better than improvement in the placebo period, greater than 5% (0 or 1 on the subjective improvement score) to calculate the 95% credit interval.

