### Rationale for setting the number of cases

In a previous study^6)^, the total trajectory lengths of healthy subjects, patients with unilateral peripheral vestibular impairment, and patients with bilateral peripheral vestibular impairment were 1.69, 2.08, and 2.17 cm (per second), respectively. Since an improvement of approximately 19% in patients with unilateral peripheral vestibular disorder and 23% in patients with bilateral peripheral vestibular disorder would be consistent with normal subjects, we consider that clinical significance would exist if there is an improvement in the total trajectory length of at least 10%, equivalent to approximately half of the 19% and 23% improvement between the placebo period and the use of this experimental device.

The Type 1 error and detection power in 1000 simulations are shown in the table below, assuming the following [1] for the total trajectory length data, based on the investigator-initiated clinical trial data. The target number of patients is set to 60 (50 enrolled and 40 complete), assuming a dropout rate of 20% and a suboptimal intensity of 15%.

Table 7. Relationship between the number of cases and detection power (%)

| Effect of treatment^*1^ | N=30 | N=40 | N=50 |
| --- | --- | --- | --- |
| 0% ^*2^ | 4.7 | 5.2% | 4.7 |
| 5% | 31.5%. | 38.2% (in the case of the | 46.1% (in the case of the |
| 7% | 55.0 | 70.6% | 78.2 |
| **10%** | **84.1%** | **91.2%** | **96.1%** |

*1 Rate of improvement in the GVS period relative to the placebo period.

*2 Rows with 0% treatment effect represent Type 1 error. The nominal significance level of 5% was confirmed to be ensured.

[1] In the investigator-initiated clinical trial data, the greatest improvement occurred immediately after stimulation (23% in Session II and 19% in Session III), and improvement rates of more than 12% existed up to 3 h later (see the Table below). To be somewhat more conservative than the investigator-initiated clinical trial data, the standard deviation of the improvement rate of the total trajectory length in the GVS and placebo periods was set to 30% and the correlation coefficient of the improvement rate between each time point to 0.3. In addition, the simulated improvement rate data were generated from a multivariate truncated normal distribution cut in the range [-80, 80]. The magnitude of the treatment effect was assumed to be constant throughout the 3 h and varied from 0%, 5%, 7%, and 10%.

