Table 8. Descriptive statistics for the percentage improvement in the total trajectory length in exploratory clinical studies as well as the correlation coefficient (%) between the rate of improvement immediately after stimulation and the rate of improvement at each time point

|  |  | Average | Standard deviation | Minimum value | Maximum value | Correlation coefficient |
| --- | --- | --- | --- | --- | --- | --- |
| Session II | |  |  |  |  |  |
|  | Immediately after stimulation | 23.1% | 14.7 | 3.1% | 49.0 | 1.00 |
|  | 30 min later | 17.1% | 14.1% | -14.3 | 44.3% | 0.49 |
|  | One h later | 16.5%. | 18.0%. | -21.1% | 52.3 | 0.53 |
|  | Two h later | 17.1% | 15.0%. | -6.3%. | 41.2 | 0.30 |
|  | Three h later | 14.8 | 11.1% | -0.9%. | 32.3 | 0.62 |
| Session III | |  |  |  |  |  |
|  | Immediately after stimulation | 19.2% | 23.6 | -25.2 | 69.5%. | 1.00 |
|  | 30 min later | 17.0%. | 22.7 | -22.5%. | 70.0 | 0.84 |
|  | One h later | 14.8 | 21.5%. | -13.1% | 70.1% | 0.74 |
|  | Two h later | 12.6%. | 25.5%. | -31.9%. | 61.3% | 0.70 |
|  | Three h later | 14.0% (1.0) | 26.3 | -43.5%. | 57.2 | 0.82 |

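### The primary mixed model has no subject-by-session effect, so its 5% level holds only if readings correlate equally within and between sessions

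*Protocol*

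**What the plan says.** Protocol section 12.2.4 defines the primary analysis. The response is the percent change in total trajectory length at five time points in each of two sessions. The fixed effects are session, device, time point, device by time point, and the two allocation factors. The random part is given as "fitting a mixed-effects model with individual effects as a variable effect". For inference, "The Kenward–Roger method is used to calculate the degrees of freedom", and the test is of "the null hypothesis that the treatment effect is 0"%. The session's own baseline is not a covariate in this model.

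Section 12.1.2 describes the simulation behind the sample size: an SD of 30%, values truncated to [-80, 80], and "the correlation coefficient of the improvement rate between each time point to 0.3". Table 7 reports type I error of 4.7/5.2/4.7% for N=30/40/50, with the note "The nominal significance level of 5% was confirmed to be ensured". Table 8 gives pilot figures for the "correlation coefficient (%) between the rate of improvement immediately after stimulation and the rate of improvement at each time point".

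A comparison at session level is planned only as a secondary analysis: "Corresponding t-tests will be performed for the difference between the mean rate of change in the total trajectory length" in the two periods.

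**The concern.** Each subject receives one device setting per session, so the treatment contrast is a difference between two session means. Section 5.1 defines the endpoint comparison in that way. Anything that shifts a whole session goes straight into that difference. Examples are the state of the subject that day and the measurement error in the baseline that all five percent changes share.

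A subject intercept absorbs what is common to all ten readings, but nothing that is specific to one session. The residual variance used for the test then comes mostly from scatter within sessions (8 of the 9 within-subject degrees of freedom). If readings in one session resemble each other more than readings in different sessions, the standard error is too small. Kenward-Roger corrects degrees of freedom and small-sample bias. It cannot supply a variance component that the model lacks.

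The single confirmatory P-value and its 95% interval are at stake.

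**Working it through.** **Inputs.** From the protocol: 5 readings per session, 2 sessions, SD 30, a correlation of 0.3 between time points, and 40 completers. A two-sided 5% test is taken from the 95% interval. The protocol does not give rb, so a range is shown.

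**1. The plan's own figures.** Applying the written model to the stated inputs for N=30/40/50 (4,000 simulated trials per cell):
- If 0.3 applies to all ten readings, type I error is 5.3/4.8/4.4%, in line with Table 7. Power for a 10% effect is 91.8/97.0/99.2%, against the stated 84.1/91.2/96.1%.
- If 0.3 applies within sessions only (rb=0), type I error is 20.1/21.6/21.5% and power 71.2/78.4/86.4%. Neither matches.

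Neither reading of the 0.3 gives both halves of Table 7 with the written model.

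**2. Variance of the contrast.** Let D be one subject's difference between session means.
- True variance: 2·SD²·[(1+4rw)/5 − rb].
- Variance the model uses: 2·SD²·[1 − (20rw+25rb)/45]/5. It averages over the 45 pairs of readings, 20 within and 25 between sessions.
- Type I error ≈ 2·[1 − Φ(1.96/√ratio)], where ratio = true/model.

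Example, rw=0.3 and rb=0.2: true bracket 2.2/5 − 0.2 = 0.240; model (1 − 11/45)/5 = 0.151; ratio 1.59; 1.96/1.26 = 1.56; type I error 12%. The standard errors are √(1800×0.240/40) = 3.29 and √(1800×0.151/40) = 2.61 percentage points.

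Results for N=40, rw=0.3:

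| rb | true | model | ratio | model SE | true SE | type I, formula | type I, simulated |
|---|---|---|---|---|---|---|---|
| 0.3 | 0.140 | 0.140 | 1.00 | 2.51 | 2.51 | 5.0% | 5% |
| 0.27 | 0.170 | 0.143 | 1.19 | 2.54 | 2.77 | 7.2% | 7% |
| 0.2 | 0.240 | 0.151 | 1.59 | 2.61 | 3.29 | 12.0% | 11-12% |
| 0.1 | 0.340 | 0.162 | 2.10 | 2.70 | 3.91 | 17.6% | 16-18% |
| 0 | 0.440 | 0.173 | 2.54 | 2.79 | 4.45 | 21.9% | 20-22% |

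Larger rw at the same rb is worse. With rb=0.3, rw=0.49 gives 0.292/0.123 = 2.37 (20%), and rw=0.78 gives 0.524/0.097 = 5.38 (40%).

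**3. Why rw > rb is expected.** To first order, a percent change is the reading error minus the baseline error. Suppose reading errors are independent with equal variance and the baseline averages k readings. A subject effect common to both sessions cancels from D, and the variance ratio becomes (1+5/k)/{[(1+5/k)+8]/9}.
- k=3: 2.667/(10.667/9) = 2.25, type I error about 19%.
- k=1: 6/(14/9) = 3.86, type I error about 32%.

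Both values of k are shown because Table 5 carries a note on three measurements at 2-minute intervals, while the stabilometry text counts one reading immediately before stimulation. Simulation with an assumed reading CV of 15% gave 20% and 34%.

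**4. After the change.** For complete data, a subject-by-session effect is equivalent to a period-adjusted test on session means. Its type I error was 4.3-5.6% in every scenario. Power for a 10% effect at N=40, rw=0.3, with truncation, was 96.5% (rb=0.3), 82.2% (0.2), 65.4% (0.1) and 52.4% (0). Without truncation it was about 84% at rb=0.2.

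**The case against.** Several counter-arguments have force.

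- **Independence.** A reader might infer that the ten readings are treated as fully independent. They are not: the subject effect models their common correlation, and with rw = rb the 5% level is held.
- **A definite loss of the 5% level.** A reader might infer that type I error is certainly several times nominal. The document does not support this, because rb is not stated. At rb=0.27 the error is only about 7%.
- **Table 7 may come from a sound analysis.** A session-level test with an assumed rb=0.27 gives type I error of 4.6/4.9/5.7% and power of about 84/93/98% for a 10% effect, close to Table 7. This does not show what was run. It does mean that one cannot claim the simulation shared the model's weakness.
- **Table 8.** It is tempting to read inflation of 20-40% from its correlations of 0.30-0.84. These are correlations with the first reading only, in 13 bilateral patients followed after a 30-minute stimulation, without a placebo session. They include differences between subjects, and only the excess of rw over rb matters.
- **Details are deferred.** Section 12 leaves details to a statistical analysis document that is not at hand and may specify a covariance structure.
- **A safeguard exists.** The paired session-mean test is pre-specified, and secondary item 5 examines the correlations. A discrepancy would be visible, but neither replaces the primary P-value.

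These points make the concern conditional. They do not remove it: the protocol states the random part of its confirmatory model, and that model is correct only at rw = rb. The shared baseline argues against that equality even when a subject-level effect is present.

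**Conclusion.** The concern holds in conditional form. Followed as written, the primary model understates the standard error whenever rw exceeds rb, and the endpoint's construction makes that likely. At the protocol's own 0.3 and N=40, the true level runs from about 5% to 21% as rb falls from 0.3 to 0.

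The confirmation of 5% in section 12.1.2 does not settle the matter, because it reports neither rb nor the fitted model. The stated 91.2% power is not shown to be wrong; it is unsupported until rb is given. The sizes rest on the assumed range of rb, complete balanced data, one constant correlation within sessions and another between them, and, for the baseline argument, independent reading errors of equal variance.

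**What to change.** - Add a random subject-by-session effect to the primary model in section 12.2.4, keeping the subject effect and Kenward-Roger.
- Use the same model wherever that section reuses it: secondary items 6 and 7, and the analyses of perimeter area, RMS and gait during stimulation.
- Keep the session-mean comparison, adjusted for period, as a supporting check. It is equivalent only for complete data. The FAS admits subjects seen in one session, and readings after a sensory-threshold breach may be left out, so it should not simply be substituted.
- State rb and the fitted model in section 12.1.2, rerun Table 7 with rw > rb, and restate type I error and power.

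No new data are needed; the model gains one variance term. The cost is a wider confidence interval and, unless rb is close to rw, lower stated power. If the statistical analysis plan already contains such a term, the protocol text need only be aligned with it and the simulation inputs completed.

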## Secondary endpoints

1. Secondary efficacy endpoints were as follows:
2. The percentage change from baseline in the outer circumference area and RMS (Root Mean Square [square root of the mean square of the distance between the mean position of all center-of-gravity sway and the measured center-of-gravity position]) values at all time points immediately after the start, after 30 min, 1 h, 2 h, and 3 h of noisy GVS
3. Percent change from baseline in the total trajectory length, perimeter area, and RMS values at all the time points 4, 5, 6, and 7 h after the start of noisy GVS
4. Ambulatory function

Percent change from baseline in the following items immediately after the start, after 1 h, 2 h, 3 h, 4 h, 5 h, 6 h, and 7 h of noisy GVS.

- - Dynamic Gait Index (DGI) short form scores^9)^ (Appendix 1)
  - Walking speed, stride length, step time, and left-right sway width during a 10-m walk measured using a gait analyzer (Walk-Mate Viewer, WALK-MATE LAB Co.

1. Subjective improvement score

- The following items immediately after the start after 1 h, 2 h, 3 h, 4 h, 5 h, 6 h, and 7 h of noisy GVS. The subject's own evaluation in 5 steps of "1: Improved, 2: Slightly improved, 3: Unchanged, 4: Slightly worsened, 5: Worsened" compared to the state before stimulation.

1. Quality of Life (QOL)

Change from baseline in the following items at 3 and 7 h after the start of noisy GVS

- Japanese version of the modified Fall Efficacy Scale (mFES) (Appendix 2)
- Japanese version of the Dizziness Handicap Inventory (DHI) (Appendix 3)

1. Activity level

- Activity (number of steps walked) from immediately after the start of noisy GVS to after 3 h and 7 h of noisy GVS.

[Rationale for the setting]

1. Because the outer circumference area and RMS are important center-of-gravital sway parameters other than the total trajectory length.
2. To compare the data before the start of noisy GVS and immediately after the end of long-term stimulation, and to examine the carry-over effect on center-of-gravity sway after the end of stimulation.
3. The DGI is a validated gait function test, to objectively measure the gait function along with the gait speed, stride length, and step time.
4. The degree of improvement as perceived by the subjects themselves is measured using a simple 5-point scale.
5. Fear of falling and dizziness will be measured using a validated quality of life questionnaire.
6. To check the correlation between the amount of activity and other assessment items.

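### The DGI short-form score is defined and analysed only as percent change from baseline, so equal point gains count differently by baseline, while mFES and DHI are analysed in points

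*Protocol*

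**What the plan says.** Section 5.2, under ambulatory function, sets one scale for the DGI short form and the 10-m walk measures: "Percent change from baseline in the following items immediately after the start, after 1 h, 2 h, 3 h, 4 h". The Protocol Summary says the same.

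Section 12.2.4, analysis of gait function tests, carries this through:

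- Descriptive statistics and t-tests: "Descriptive statistics will be calculated for the percentage change from baseline in the gait test endpoints (DGI score, walking speed at 10-m gait".
- Model: "The same model as the main analysis for the primary endpoints will be used for the percent change in the perimeter area, RMS values", with the gait endpoints, DGI included, listed in the same sentence. The terms given for the primary model are session, device, time point, device by time point, the two allocation factors and a subject effect. Baseline DGI is not among them.
- The plots over time and the correlations with total trajectory length also use percent change for the gait endpoints.

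The questionnaire scores are handled differently. Section 5.2 defines mFES and DHI as "Change from baseline in the following items at 3 and 7 h after the start of noisy GVS". Section 12.2.4 follows: "Descriptive statistics will be calculated for the change from baseline in the mFES score, DHI score, and DHI subscale scores", and then "An analysis of covariance will be performed using the mFES score, DHI score, and DHI subscale scores at 3 and 7 h", with baseline as an explanatory variable.

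The last item of section 12.2.4 plans a posterior probability for each secondary endpoint, with the limit "greater than 5% (0 or 1 on the subjective improvement score) to calculate the 95% credit interval".

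**The concern.** Walking speed, stride length, step time and sway width are physical measurements, for which a ratio to baseline is a usable scale. The DGI is a score. Dividing its change by the baseline score makes the mean depend on who gained the points as well as on how many were gained. The protocol gives no reason for treating this score like a speed when its other scores stay in points. It also supplements percent change for total trajectory length with raw values, absolute change and a model for absolute change, and offers none of these for the DGI.

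Section 5.2 justifies the DGI as a validated gait test, so it is one of the links from sway to function. What is at stake is whether its result can be read as a defined amount of gait improvement.

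**Working it through.** The plan states no figure for this point, so there is nothing to reproduce. The check is arithmetic on the scale.

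**Inputs.** The DGI short-form range is not visible (the content of Appendix 1 is not shown), so 0-12 is assumed, with 0-24 as a second case. The DHI has 25 items scored 0, 2 or 4 (Appendix 3), giving 0-100. No baseline DGI distribution is given, so the baselines below are illustrative.

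**Step 1: one point as a percentage.** Percent change = 100 × points gained / baseline.

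| Baseline DGI | One-point gain |
| --- | --- |
| 3 | 100/3 = 33.3% |
| 4 | 100/4 = 25.0% |
| 6 | 100/6 = 16.7% |
| 8 | 100/8 = 12.5% |
| 11 | 100/11 = 9.1% |
| 23 (0-24 range only) | 100/23 = 4.3% |

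From 3 to 11 the weight of one point differs by 33.3/9.1 = 3.7 times. On the 0-24 range, from 3 to 23, it differs by 23/3 = 7.7 times. At a baseline of 0 the value does not exist.

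**Step 2: does the crossover remove this?** No. If a patient has the same baseline B in both sessions, the within-patient difference is (score under GVS − score under placebo)/B. The weight 1/B remains.

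**Step 3: effect on a mean.** Take 40 patients, 20 at baseline 4 and 20 at baseline 10.

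- One point gained only by the low half: mean 0.5 points; mean percent change (20 × 25% + 20 × 0%)/40 = 12.5%.
- One point gained only by the high half: mean 0.5 points; mean percent change (20 × 0% + 20 × 10%)/40 = 5.0%.
- One point gained by the low half and two lost by the high half: mean (20 × 1 − 20 × 2)/40 = −0.5 points; mean percent change (20 × 25% − 20 × 20%)/40 = +2.5%. The sign reverses. This pattern is constructed to show that reversal is possible.

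**Step 4: the 5% posterior threshold.** mFES and DHI are not percent-change endpoints, and activity is a step count with no baseline. For the DHI, 5% of baseline is 0.05 × 20 = 1 point at baseline 20 and 0.05 × 80 = 4 points at baseline 80. Read as 5% of the range it is 0.05 × 100 = 5 points. The text does not say which is meant.

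**The case against.** The strongest case against is that the consequence is limited. The DGI is one of many secondary measures, gait tests are done only when possible, and each patient is compared with himself or herself. The scale introduces no demonstrated bias and no inflation of type I error; it changes how patients are weighted. The DGI range and the baseline distribution are not visible. Patients who cannot walk independently are excluded, so baselines near 0 may be rare. All of that stands, and it sets the size of the point. It does not give a reason for percent change.

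It may also be said that details belong in the statistical analysis plan. That is fair for the unit of the 5% threshold. It is not fair for the DGI scale, which the protocol itself fixes in the endpoint definition and the analyses.

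A reader might infer four stronger things that the document does not support:

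- That the QOL results also depend on percent of baseline. They do not: mFES and DHI are tested as change and modelled with baseline adjustment. Only their supplementary posterior probability is touched.
- That the 5% limit applies to every secondary endpoint. The subjective improvement score has its own limits of 0 or 1.
- That those limits run the wrong way because 1 means improved and 5 worsened. The sentence speaks of improvement under GVS against improvement under placebo, so 0 or 1 can be read as the size of an improvement. The direction is unstated, which is not the same as wrong.
- That any one-point DGI gain passes 5% automatically. The analysis refers back to the posterior of a mean treatment effect. At an assumed mean baseline of 8, 5% is 0.05 × 8 = 0.4 points on average, which is not automatic. On a 0-24 range a single point at baseline 23 is only 4.3%.

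**Conclusion.** The point holds for the DGI. The protocol fixes this score as percent change only, without a baseline term, and treats it differently from its other scores. Equal point gains are weighted by the inverse of baseline, about 3.7-fold between baselines 3 and 11 on an assumed 0-12 range and 7.7-fold between 3 and 23 on an assumed 0-24 range. The actual distortion depends on the DGI range and the spread of baselines, neither of which is visible. It is a weakness of scale in a secondary endpoint and leaves the primary conclusion untouched.

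The missing unit of the 5% threshold for mFES, DHI and step count is real but minor, because it affects only a supplementary summary.

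**What to change.** In the Protocol Summary, section 5.2 and section 12.2.4 (gait analysis and correlations), define the DGI endpoint as change from baseline in points. Fit the planned mixed model to it with baseline DGI added as a covariate. Keep percent change for walking speed, stride length, step time and sway width.

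In the posterior-probability item of section 12.2.4, or in the statistical analysis plan, state the threshold in points for DGI, mFES and DHI and in steps for activity, and state which direction of the subjective score counts as improvement.

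The cost is wording and one model term; the data collected do not change. The downside is that the DGI result no longer sits on the percent scale of the other gait measures.
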